#### 9.4.3 ANALYSIS OF THE SECONDARY ENDPOINT(S)

**Aim 3:** *To determine predictors of outcomes after surgical treatment of DRFs in the elderly.* We will assess the effect of potential predictors of outcomes within each surgical treatment group and assess whether the effect remains the same across the treatment groups. Potential predictors are variables found to be associated with post-surgical outcomes in our previous studies and include fracture severity, reduction adequacy (measured, for example, using intra-articular step-off for intra-articular fractures), age, income level, baseline activity level and bone mineral density. The analysis will initially be done separately in the three surgical groups using the linear mixed-effects models and 12-month outcomes. Other variables potentially associated with outcome variation are pre-existing arthritis, extensive soft-tissue injury, presence of nerve injury, presence of other associated injuries and whether the dominant hand is injured. Although some of the proposed potential predictors are likely to be collinear, we do not have two variables that are highly collinear on face value. We will, however, assess multi-collinearity and employ data reduction strategies to reduce the number of variables. In a separate model, we will also consider 6-week values of the outcome variable as a potential predictor of long-term outcome. Within each surgical group, other variables will be considered such as an indicator for additional fixation requirement using additional plates or screws as a part of the VLPS placement, because the added fixation procedures may indicate a more severe fracture pattern. For continuous variables such as age, we will explore a proper functional relationship using age categorical indicators and splines. If the models for each surgical group show similar relationships between predictors and outcome variables, we will combine the data across the surgical groups. We do not have a hypothesized differential effect of a predictor on outcomes that depend on surgical group, and thus interactions will be explored only if a large difference in the relationship between a predictor and outcomes are observed between any two surgical groups. Similar analyses will be done using secondary outcome variables of interest.

**Aim 4:** *To compare the 12-month post-surgical outcomes and 24-month recovery trends of patients who have chosen not to have surgery with patients within the surgical arm.* Many elderly patients have low functional demands and can tolerate the deformity that almost certainly results following closed reduction. Therefore we will compare the long-term outcomes and the trends between the surgical and non-surgical groups. For a valid comparison, it will be essential to account for baseline differences that would potentially result in treatment choices and outcome differences. This will be done using propensity score (PS) method and the inverse-probability treatment weighted (IPTW) method. The goal of both methods is to estimate the outcome differences between the surgical and non-surgical groups at 12 months, adjusting for selection bias using the measured potential confounding variables. In the PS method, we will calculate the propensity for choosing to have surgery, evaluate the distribution of the estimated propensity scores and perform the comparison stratified by the propensity quintiles. We will estimate the propensity scores using a logistic regression model with surgical group as the dependent variable. The propensity model will not be parsimonious and will include as predictors all

demographic and other baseline variables, in particular those representing preference toward choosing surgery such as physical activity level prior to fracture. The stratified comparison between the surgical groups combined and the non-surgical group will be done using a linear mixed-effects model with the 12-month MHQ score as the dependent variable and the propensity quintiles as the strata, after trimming. The model will include site as random-effects to adjust for within-site correlation and an indicator for surgical groups; the parameter estimate for the indicator will estimate the outcome difference between the surgical and non-surgical groups. For the IPTW method, a similar linear mixed-effects model will be fit, but using the inverse of the estimated probability-of-treatment as weights in which the probability-of-treatment is estimated from the propensity model. The linear mixed-effects model can still include baseline covariates that may affect the outcome differences. Lastly, we will visualize the outcome trends between the four groups over the 24-month period and model the long-term differences. The longitudinal outcome model will also include time and an interaction of time by the surgical groups. If the trends appear to differ across all four groups, richer parameterization will be done as needed; the analytic approach for trend comparison in hand outcomes during follow-up will generally be similar to the Aim 2 analytic plan.

Aim 5: To conduct a cost-utility analysis comparing the three treatment arms with the nonsurgical arm. To calculate QALYs for a cost-utility analysis, we have already begun development and initial testing of an online time trade-off (TTO) survey to determine utility for various health states related to DRF. Utility is the preference assigned to a particular health state on a scale where 0 represents death and 1 represents perfect health. Using the TTO method, a person is asked to choose how much time in his/her life he/she is willing to give up to be in a healthier state while avoiding a less healthy one. We will assess the utilities for different health states that could occur (malunion, nonunion, infection, etc) following DRF treatment. Data from the current study will be used to determine the outcomes and complications of DRFs. QALYs will then be calculated from the utilities, adjusted for years of life remaining for different age groups. We will also obtain utilities of elderly subjects from the community for a comprehensive analysis of the societal perspective, as recommended by the Panel on Cost Effectiveness in Health and Medicine. Medical costs will be assessed using the relevant charges/cost data for the procedures on all participants recruited at the Michigan Medicine. The costs of lost productivity will be valued as the average US hourly wage, as obtained from the US Bureau of Labor Statistics, of a person most likely to be affected by a DRF, multiplied by the average time to healing, as obtained from this study. Costs will be discounted at a rate of 3%. Sensitivity analyses will be done to change the assumptions to fit the extremes of these estimates. If, in changing these estimates, the results are similar, we can be assured of the stability of the conclusions. One- and two-way sensitivity analyses will be performed to determine the stability of the incremental cost-utility ratio, which will incorporate the cost and utility range of the study subjects' in the calculations

---

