## 9.2 SAMPLE SIZE DETERMINATION

We propose to randomize 474 patients to one of three surgical arms (158 per surgical arm). We will follow another 158 non-surgical patients meeting the inclusion/exclusion criteria. Sample size was determined to have adequate power for Aim 1 based on the primary outcome of the MHQ summary score at 12-month follow-up. **We expect to have complete data for 12-month follow-up time from 126 patients in each group, after accounting for a conservatively estimated 20% decrease in sample size from losses to follow-up.** For Aim 1, we expect 126 patients per group to give 80% power to detect an 8 point difference in the mean MHQ summary scores between VLPS and CRP and between VLPS and EFP using a mixed-effects model with a two-sided 0.025  $\alpha$ -level test. This assumes a standard deviation (SD) of 18 points (corresponding to an effect size of 0.44 SD), an average of 24 patients per site and an intra-site correlation coefficient (ICC) of 0.012. **To adjust for potential within surgeon correlation, we will also consider either a three level hierarchical model with surgeons nested within site, or use surgeons instead of sites as random intercepts. If technical variation is mostly between surgeons, addressing within surgeon correlation will reduce the ICC, which would give larger power to detect the same effect size. Covariate adjustments will likely give greater power by reducing the variability when the covariates are associated with the outcome and are not highly correlated with other covariates in the model.** We expect the 8 point difference in MHQ score at 12-months as a minimally detectable and meaningful difference between VLPS and either CRP or EFP. Our retrospective study of patients treated with VLPS showed mean ( $\pm$ SD) MHQ scores of 77 ( $\pm$ 15) at 3 months, 81 ( $\pm$ 17) at 6 months, and 85 ( $\pm$ 18) at 12 months for elderly patients. We believe the observed improvement of 8 points from 3 to 12 months to be similar to the expected post-surgical improvement difference between VLPS surgery compared with either EFP or CRP.

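### The Aim 4 IPTW analysis names an inverse-probability-weighted linear mixed model but no variance method suited to such weights; default model standard errors would make its confidence interval too narrow

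*Protocol*

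**What the plan says.** Section 9.2 plans the group sizes: "We propose to randomize 474 patients to one of three surgical arms (158 per surgical arm", and "We will follow another 158 non-surgical patients meeting the inclusion/exclusion criteria". After the assumed 20% loss it expects 126 patients with 12-month data in each group.

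Section 9.4.3, Aim 4, sets out two methods that "estimate the outcome differences between the surgical and non-surgical groups at 12 months, adjusting for selection bias".

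- **Quintile stratification.** A linear mixed model for the 12-month MHQ score, with "the propensity quintiles as the strata, after trimming". On dependence, "The model will include site as random-effects to adjust for within-site correlation".
- **IPTW.** Here "a similar linear mixed-effects model will be fit, but using the inverse of the estimated probability-of-treatment as weights". The weights are the plain inverse of the fitted probability. Stabilisation is not mentioned, and trimming is stated only for the quintile analysis. "The linear mixed-effects model can still include baseline covariates that may affect the outcome differences".

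Both use one logistic propensity model: "The propensity model will not be parsimonious and will include as predictors all" demographic and other baseline variables. The section says that the coefficient of the surgical indicator estimates the difference. It does not say how the standard error, interval or p-value of the IPTW estimate is obtained. No alpha is stated for Aim 4.

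**The concern.** In a linear mixed model, a weight w ordinarily declares that the observation has residual variance σ²/w. A casting patient whose propensity for surgery is 0.75 has casting probability 0.25 and weight 4, and the fit treats that patient as measured with a quarter of the variance. An inverse-probability weight carries no such information. It only says how many patients in the target population this one stands for. The point estimate is fine, but the default standard error is not, and a site random intercept does not repair it.

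The stake is the interval around one of the two confounding-adjusted estimates of surgery against casting. That comparison is part of the primary objective in section 3, although it is analysed among the secondary endpoints. Because the quintile analysis uses no weights, the two methods could also appear to differ in precision for a purely technical reason.

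**Working it through.** **Reproducing the plan's own figure.** The protocol gives no error rate or standard error for the IPTW test. The nearest stated figure is the Aim 1 sample size. For 8 points, SD 18, two-sided 0.025 and 80% power, a two-sample calculation gives 97 per group. The site design effect is 1 + (24 − 1) × 0.012 = 1.276, and 97 × 1.276 = 123.8, close to the stated 126. Also 158 × 0.8 = 126.4. The planning inputs therefore hang together and are used below.

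**Inputs from section 9.2.** 474 surgical and 158 casting patients (3:1); 378 and 126 with 12-month data, N = 504; SD 18; ICC 0.012.

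**Assumed, not in the protocol.** Two-sided 5% for Aim 4, default model standard errors, the spread of the propensity, and the strength of the covariates.

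**Step 1: no selection, constant propensity 0.75, unstabilised weights.**

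- Weights are 1/0.75 = 1.33 (surgical) and 1/0.25 = 4 (casting), so each group's weights sum to N.
- The average weight is 2, so the fitted weighted residual variance is about 2σ². Each weighted mean gets model variance 2σ²/N, and the difference gets 4σ²/N.
- The true variance is σ²/(0.75N) + σ²/(0.25N) = 5.33σ²/N.
- The SE ratio is √(4/5.33) = 0.866, about 13% too small.
- Actual rejection is 2 × [1 − Φ(1.96 × 0.866)] = 9.0%.
- In points, ignoring the small ICC, the model SE is 18 × √(4/504) = 1.60 and the true SE is 18 × √(5.33/504) = 1.85.

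**Step 2: unequal weights among casting patients.** Let D be the weighting design effect in that group. The true variance becomes (1.33 + 4D)σ²/N while the model still reports 4σ²/N.

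| D | SE ratio | Rejection at nominal 5% |
|---|---|---|
| 1.0 | 0.866 | 9% |
| 1.2 | 0.808 | 11% |
| 1.5 | 0.739 | 15% |
| 2.0 | 0.655 | 20% |

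**Step 3: simulation under a true null.** 504 patients, 24 sites, ICC 0.012, SD 18, ten covariates, logistic propensity re-estimated in each run, weighted random-intercept REML fit, 800 runs per scenario. The rows below have covariates in the outcome model explaining 20% of MHQ variance, and no trimming. SEs are in MHQ points. Robust means a site-clustered sandwich variance on the same fits.

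| Weights | C-statistic | Mean model SE | Actual SE | Rejection, model SE | Rejection, robust SE |
|---|---|---|---|---|---|
| Unstabilised | 0.66 | 1.42 | 1.79 | 12.1% | 6.1% |
| Unstabilised | 0.76 | 1.42 | 2.05 | 17.3% | 6.3% |
| Unstabilised | 0.83 | 1.43 | 2.47 | 24.8% | 9.9% |
| Stabilised | 0.59 | 1.65 | 1.59 | 4.6% | 3.1% |
| Stabilised | 0.66 | 1.65 | 1.93 | 9.8% | 8.5% |
| Stabilised | 0.76 | 1.66 | 2.09 | 12.5% | 6.9% |
| Stabilised | 0.83 | 1.68 | 2.54 | 20.4% | 8.6% |

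Across all untrimmed unstabilised scenarios with model SEs, rejection was 6.0% to 10.8% at C 0.59, 11.5% to 12.4% at C 0.66, 13.5% to 17.3% at C 0.76, and 21% to 31% at C 0.83. The 31% includes 1.5 points of residual bias, so it is not a pure variance effect. With trimming and truncation the range was 6.1% to 18.6%. A second simulation of 1,500 runs per scenario gave 17% to 25% at a C-statistic of about 0.80.

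**The case against.** The strongest reply is that the protocol never says default standard errors will be used. A weighted mixed model and a robust variance are compatible, and the choice of variance estimator for an observational secondary analysis is commonly left to the statistical analysis plan, which is not at hand. The protocol also cites a methods paper on marginal structural models for IPTW, and the documents do not show what variance that paper uses. All of this stands, and it is why the point is conditional. It does not dispose of the point. The protocol fixes the model class, the random effect and the form of the weights, and the usual output of exactly that combination is not valid for these weights. For multiple imputation, section 9.4.2 does state how the variance is handled; the IPTW paragraph has no counterpart.

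Three stronger readings are tempting and are not supported:

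- A reader might infer that the test rejects a true null two to four times too often, as a fact of the plan. That multiple depends on propensity spread, covariate strength, alpha and weight form, none of which is given for Aim 4 except that the wording points to unstabilised weights. With stabilised weights and constant propensity every weight is 1, the model variance is the correct 5.33σ²/N, and the inflation is nil.
- A reader might infer that the whole surgery-versus-casting comparison is affected. The quintile analysis uses no weights and is not.
- A reader might extend the point to the 24-month trend models. The protocol plans no weights there.

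**Conclusion.** The point holds in conditional form. Run as written, and read from its default output, the IPTW model gives too narrow an interval. The 13% shortfall in the standard error and the 9% rejection rate need only the protocol's 3:1 split, the literal unstabilised weights, default standard errors and an assumed 5% level. The wider range of about 6% to 25% rests on assumed C-statistics of about 0.6 to 0.8. It shrinks with stabilised weights, to 3.8% to 6.5% at C 0.59. This is worth correcting before analysis, but it touches one of two methods for a secondary aim and leaves the randomised comparisons of Aim 1 alone.

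**What to change.** Add to section 9.4.3, Aim 4, after the IPTW model: *Standard errors and confidence intervals for the IPTW estimate will come from a site-clustered sandwich estimator, or from a bootstrap that re-estimates the propensity model in each resample. The default standard errors of the weighted mixed model will not be used.* Choose one of the two in advance. It would also help to state whether the weights are stabilised and whether trimming applies to this analysis.

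The cost is one or two sentences, a few lines of code and a wider interval. The remedy has limits. In the simulations the sandwich gave 3.4% to 6.3% rejection for unstabilised, untrimmed weights up to C 0.76, but 6.0% to 9.9% at C 0.83. Robust errors do not remove residual confounding bias when propensity separation is strong. The bootstrap was not simulated.

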| Study Description:                                      | The goal of this 24-center randomized controlled trial is to compare the physical, functional and quality of life outcomes of three different surgical methods for treating distal radius fractures in the elderly: close reduction and percutaneous pinning (CRPP), external fixation with or without percutaneous pinning (EFP) and internal fixation with volar locking plates. We will also follow a cohort of patients who opt for the non-surgical treatment, close reduction and casting, to examine and compare the same outcomes following non-surgical treatment. |
| Objectives:                                             | 
Primary Objective: To compare outcomes of DRFs in patients age 60 years and older treated with VLPS with those treated with EFP, CRPP, and casting
 
Secondary Objectives: to compare the trend of recovery for DRFs treated with VLPS with the other fixation techniques and to determine predictors of outcomes
                                                                                                                                                                                                                                               |
| Endpoints:                                              | 
Primary Endpoint: Michigan Hand Outcomes Questionnaire Summary score at 12-month assessment
 
Secondary Endpoints: Michigan Hand Outcomes Questionnaire Subdomain scores, SF-36, RAPA, hand strength, wrist range of motion
                                                                                                                                                                                                                                                                                                                                     |
| Study Population:                                       | Community-dwelling adults age 60 years or older presenting to participating sites' emergency or urgent care department with isolated closed distal radius fracture                                                                                                                                                                                                                                                                                                                                                                                                          |

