#### 9.4.9 EXPLORATORY ANALYSES

Aim 5: To conduct a cost-utility analysis comparing the three treatment arms with the nonsurgical arm. To calculate QALYs for a cost-utility analysis, we have already begun development and initial testing of an online time trade-off (TTO) survey to determine utility for various health states related to DRF. Utility is the preference assigned to a particular health state on a scale where 0 represents death and 1 represents perfect health. Using the TTO method, a person is asked to choose how much time in his/her life he/she is willing to give up to be in a healthier state while avoiding a less healthy one. We will assess the utilities for different health states that could occur (malunion, nonunion, infection, etc) following DRF treatment. Data from the current study will be used to determine the outcomes and complications of DRFs. QALYs will then be calculated from the utilities, adjusted for years of life remaining for different age groups. We will also obtain utilities of elderly subjects from the community for a comprehensive analysis of the societal perspective, as recommended by the Panel on Cost Effectiveness in Health and Medicine. Medical costs will be assessed using the relevant charges/cost data for the procedures on all participants recruited at the Michigan Medicine . The costs of lost productivity will be valued as the average US hourly wage, as obtained from the US Bureau of Labor Statistics, of a person most likely to be affected by a DRF, multiplied by the average time to healing, as obtained from this study. Costs will be discounted at a rate of 3%. Sensitivity analyses will be done to change the assumptions to fit the extremes of these estimates. If, in changing these estimates, the results are similar, we can be assured of the stability of the conclusions. One- and two-way sensitivity analyses will be performed to determine the stability of the incremental cost-utility ratio, which will incorporate the cost and utility range of the study subjects' in the calculations

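### Aim 5 sets the surgical arms against a self-selected casting cohort using trial outcomes, complications and healing time, with no control for selection, although Aim 4 treats such control as essential for the same contrast

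*Protocol*

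**What the plan says.** - **How the casting group arises.** Synopsis (Section 1.1): "We will also follow a cohort of patients who opt for the non-surgical treatment, close reduction and casting". Only the three surgical techniques are randomised.
- **What Aim 5 compares.** Section 9.4.9 gives the aim as: "To conduct a cost-utility analysis comparing the three treatment arms with the nonsurgical arm". Section 9.4.3 carries the same text, and Section 3 lists the objective as tertiary/exploratory.
- **What the trial supplies.** Section 9.4.3, Aim 5: "Data from the current study will be used to determine the outcomes and complications of DRFs". Lost productivity is an average US wage "multiplied by the average time to healing, as obtained from this study".
- **What does not come from participants' own outcomes.** Utilities are time trade-off values for health states, supplemented by a community sample. Medical costs are procedure charges or costs at one centre.
- **Sensitivity analyses.** Estimates are moved to their extremes, with one- and two-way variation over cost and utility ranges. If results change little, the conclusions are to be taken as stable.
- **What Aim 4 says of the same groups.** "For a valid comparison, it will be essential to account for baseline differences that would potentially result in treatment choices and outcome differences". The method follows: "This will be done using propensity score (PS) method and the inverse-probability treatment weighted (IPTW) method".
- **Where that method is spelled out.** "The stratified comparison between the surgical groups combined and the non-surgical group will be done using a linear mixed-effects model", "with the 12-month MHQ score as the dependent variable and the propensity quintiles as the strata, after trimming".

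**The concern.** Patients who decline surgery are likely to differ from those who accept randomisation. Aim 4 itself names physical activity before the fracture as a marker of preference for surgery. If such traits also affect complications, the health states reached or the speed of healing, casting and surgical patients will differ on Aim 5's inputs even where treatment makes no difference.

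The protocol recognises this for the hand-outcome score and, one aim later, is silent on it for the economic inputs. The casting ratios would then stand beside the randomised three-arm ratios with nothing to mark that one set is protected by randomisation and the other is not. This matters because Aim 5 is meant to identify a dominant strategy, and the background section on economic analysis points to health policy as the audience.

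**Working it through.** The plan attaches no figure to this point, so there is none to reproduce. The check sets the texts side by side and then uses a small illustration.

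**Step 1: does Aim 4's adjustment reach Aim 5's inputs?**

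| | Aim 4 | Aim 5 |
|---|---|---|
| Groups | Surgical arms pooled v casting (12-month model) | Each surgical arm v casting |
| Quantity | 12-month MHQ score | Outcome and complication frequencies, time to healing, QALYs, costs |
| Control for selection | Propensity quintiles and IPTW | None stated |
| Cross-reference to the other aim's adjustment | – | None |

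An adjusted pooled MHQ difference does not yield arm-specific complication or health-state probabilities, or healing times. Aim 4 as written therefore does not supply adjusted inputs to Aim 5.

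**Step 2: which inputs are exposed?** Health-state and complication frequencies and average time to healing come from trial participants and are exposed. Procedure charges and the average wage depend little on who chose casting. A time trade-off value attaches to a health state, so it is the same whichever group the patient is in.

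**Step 3: illustration, all inputs assumed.** Let treatment have no effect. Let a share p of each group be low-activity, with poor-state risk r1 in low-activity patients and r0 in the others.

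- Crude rate in a group = (1 − p) × r0 + p × r1.
- Crude difference, casting minus surgery = (p_cast − p_surg) × (r1 − r0).
- Assumed: p_surg = 0.33, p_cast = 0.40 to 0.60, r0 = 0.10, r1 = 0.20 to 0.30.
- Smallest: (0.40 − 0.33) × (0.20 − 0.10) = 0.007.
- Largest: (0.60 − 0.33) × (0.30 − 0.10) = 0.054. Check: surgery 0.67 × 0.10 + 0.33 × 0.30 = 0.166; casting 0.40 × 0.10 + 0.60 × 0.30 = 0.220.

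Selection alone gives a gap of 0.7 to 5.4 percentage points. If low-activity patients were rarer in the casting group, the sign would reverse.

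**Step 4: would the planned sensitivity analyses show it?** Take the 5.4-point gap, an assumed disutility of 0.1 and an assumed 2-year horizon: 0.054 × 0.1 × 2 = 0.0108 QALY. Halving the disutility gives 0.0054 and doubling it gives 0.0216. The sign never changes, so the result looks stable although the true effect here is zero. Varying costs and utilities leaves the unequal patient mix untouched.

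**The case against.** **Silence is not a stated method.** A reader might infer that the protocol commits to crude group data. It does not say so, and an SAP or economic plan that is not shown could add adjustment. That is fair, and the point is put as an omission. It is still more than detail left for later. The protocol describes Aim 5 at length (utility source, trial inputs, cost source, wage valuation, 3% discounting, sensitivity analyses), requires adjustment for the same contrast one aim earlier, and draws a stability conclusion that cannot cover confounding.

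**The requirement is written under Aim 4.** True, but the groups and the way they were formed are the same.

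**Shared eligibility.** Section 9.2 has casting patients meet the same criteria as randomised patients. This narrows differences in fracture type and comorbidity, but not differences in preference or functional demand.

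**The size is easily overstated.** A reader might infer that selection could outweigh the treatment benefit several times over and reverse the ranking. For example, an assumed patient-level utility gap of 0.02 to 0.05 over 2 years is 0.04 to 0.10 QALY, against 0.1 × 0.25 year = 0.025 for an assumed earlier recovery, a ratio of 1.6 to 4. The documents do not support this. Under the time trade-off method in 9.4.3 and 9.4.9, a patient's own pre-existing utility does not enter the QALY. The gap would enter only with the SF-36-derived utilities named in Section 3, which is not the method those sections describe. Through state frequencies, the assumed 0.7 to 5.4 points give 0.007 × 0.1 × 2 = 0.0014 to 0.054 × 0.1 × 2 = 0.0108 QALY, and even that rests on assumed inputs and horizon.

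**Remedies that go further** would exceed the stated method, such as adjusting QALYs for baseline SF-36 or making the three-arm comparison the main result. They are not proposed.

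**Conclusion.** The concern holds in a limited form. As written, Aim 5 takes outcome and complication frequencies and healing time from trial data for a self-selected cohort, states no control for selection, and relies on sensitivity analyses that cannot reveal it. The surgery-versus-casting ratios can therefore be confounded, and the stability statement does not hold for them. The ratios among VLPS, EFP and CRP are protected by randomisation.

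Neither the size nor the direction of the bias can be derived from the document. The illustrative figures show the mechanism and are not estimates. The conclusion assumes only that traits driving the choice of casting also affect the trial-derived inputs, which Aim 4 already takes to be possible for outcomes. Severity is low: the aim is tertiary/exploratory and the primary analysis is unaffected.

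**What to change.** In Sections 9.4.3 and 9.4.9, add under Aim 5 that:

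1. for the casting comparison, health-state and complication probabilities and time to healing will be estimated with the Aim 4 propensity/IPTW weights, applied to casting versus each surgical arm. Because the surgical arms are randomised, the planned surgery-versus-casting propensity model can serve each of them;
2. the result will be labelled observational and reported separately from the randomised three-arm comparison;
3. the statement on stability refers to variation in costs and utilities and does not cover confounding.

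The propensity model is already planned, and its baseline variables, including RAPA, are collected at enrolment. The cost is a wider interval for the casting comparison and a little more analysis. Weighting deals only with measured differences, which is why the observational label is needed as well.
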